We hypothesise that, in comparison to treatment with clobazam, corticosteroids are more effective in improving cognitive performance and EEG abnormalities in children with encephalopathy with ESES. Based on previous studies, the difference in percentage of responders is estimated at around 25% [19]. The use of corticosteroids may be associated with more frequent or more severe side effects than clobazam.

In a multicentre randomised controlled trial with 1:1 allocation to corticosteroids and clobazam, we aim to assess whether one of the treatments is superior to the other. The following study objectives and hypotheses are addressed in a population of recently diagnosed patients with encephalopathy with ESES:

*Primary study objective*
To compare the effects of treatment with corticosteroids or clobazam on cognition at 6 months after start of the treatment.

*Secondary study objectives*
To compare the effects of treatment with corticosteroids or clobazam on sleep-induced epileptiform activity, measured as the spike wave index (SWI), in the patients’ sleep EEG.To compare the effects of treatment with corticosteroids or clobazam on the frequency of any concomitant seizures.To compare the side effects and tolerability of corticosteroids and clobazam.To compare the effects of treatment with corticosteroids and clobazam on subjective daily functioning, as measured with a visual analogue score (VAS).To assess demographic and disease-related biomarkers, including immunological biomarkers, as potential predictors of disease activity and response to treatment with corticosteroids or clobazam.

The study is conducted as a randomised open-label parallel-group controlled trial with 1:1 treatment allocation to clobazam and corticosteroid treatment arms and is aimed at proving superiority of one treatment over the other. The trial also uses a pragmatic approach, whereby participating investigators will be allowed to apply, within predetermined limits, the dosing schedules which they consider best according to their judgement and patient response. The same flexibility will also apply to the option of using i.v. versus oral steroids, which will be left to the discretion of the treating physicians.

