### Cytokine profiles and autoantibodies at baseline and 8 months after start of treatment (2 months after withdrawal of study steroids, to limit the influence of a possible decrease in levels caused solely by treatment)

A snapshot of around 100 cytokines will be analysed (Luminex, X-map technology) in serum of the study participants, (a) at randomisation and (b) 8 months after start of treatment (2 months after withdrawal of corticosteroids). Screening for autoantibodies will be performed using rat brain immunohistochemistry, optimised for extracellular antigens, like NmDAR, AMPaR, GAD, GABABR, LGI1, and Caspr2 [24]. In addition, all samples will be tested by in-house cell-based assays for anti-NMDAR and anti-GlyR antibodies. Samples with positive staining, but no known antibodies, will be tested by immunocytochemistry using live hippocampal neurons. If positive, immunoprecipitation will be the first step towards antigen discovery. The laboratory analyst is blinded for treatment.

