### Statistical analysis

The primary analyses will be performed according to the intention-to-treat principle. We will also perform (secondary) analyses in patients who have completed their assigned treatment for the period of 6 months.

Continuous outcomes will be presented with means and 95% confidence intervals. These outcomes will primarily be compared between the two treatment groups using a *t* test or Mann-Whitney *U* test depending on the distribution of the data (normal vs not normal). Categorical outcomes will be presented as proportions with 95% confidence intervals. These outcomes will primarily be compared between the two treatment groups using Fisher’s exact test. Rates of (serious) adverse events will be compared in terms of risk ratios with corresponding 95% confidence intervals. We will also identify the proportion of patients that continue on the initially allocated treatment throughout the entire study period, and analyse possible predictors for discontinuation.

Although the stratified randomisation procedure intends to create two groups with equal patient characteristics, it is known that in randomised trials of < 1000 patients, there still is a risk of bias by chance [25]. Adjusted analyses are often performed to reduce the influence of the possible differences between the two treatment arms [26]. Therefore, possible predictors of treatment outcome (i.e. known prognostic factors) will be included in a multivariate logistic/linear regression model. These prognostic factors are as follows: age at ESES recording, time interval between ESES recording and inclusion, IQ levels and cognitive sum scores at enrolment, number of drugs administered before enrolment, and aetiology (unknown, structural, metabolic, genetic, immune, infectious). We will also include cytokine and autoantibody profiles as possible predictors.

The prospective design and structured follow-up schedule should minimise the amount of missing data. However, to account for possible influence of missing data, we will perform a sensitivity analysis using multiple imputation methods [27].

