### Sample size calculation

A formal sample size calculation is hampered by the fact that no previous trials with these interventions have been performed. Our recently performed meta-analysis of published cases with epileptic encephalopathy with ESES provides the basis for estimating the difference in proportions of successfully treated patients that might be expected between corticosteroids and benzodiazepines. In our meta-analysis, treatment success was defined as improvement in EEG (at least 25% decrease in SWI) or cognition (10 IQ points or improvement defined by author). Differences in proportions were 25–30% between the two treatment groups in favour of corticosteroids. However, these results are of limited value because of the small sample size in the included studies and their mostly retrospective design.

In the RESCUE ESES study, we aim to include a total of 130 children, of whom 65 will be randomised to treatment with corticosteroids and 65 to clobazam. This sample size permits to detect a difference of 25% in the proportion of successfully treated patients between the two treatment arms (for example 50% vs 25%). In fact, 116 patients are needed to identify this difference with a power of 80% and a two-sided alpha of 5%, and we additionally account for a possible dropout rate of 10%.

As mentioned above, success is defined as improvement of 0.75 of the standard deviation of either IQ or the cognitive sum score. Differences of this magnitude have been reported in earlier observational (non-randomised) studies in this area [28]. Displaying the primary outcome as a dichotomous value (instead of a continuous value) will lead to a conservative estimation of the difference in effect. Therefore, our sample size calculation is likely to be an overestimation of the required number of patients for the continuous outcomes.

For continuous outcomes, we can detect standardised mean differences or Cohen’s *d* of around 0.5 (power = 80%, two-sided alpha of 5%). For Cohen’s *d*, an effect size of 0.2 to 0.3 is considered a “small” effect, around 0.5 a “medium” effect, and above 0.8 a “large” effect [29]. This means that “medium” effects on secondary outcomes can be detected by our trial including 130 children. Furthermore, as the primary outcome can also be displayed as a continuous variable (IQ or cognitive sum score), this also applies to analysis of the primary outcome as a continuous variable.

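### One secondary regression model is asked both to adjust the treatment effect and to assess cytokine and autoantibody predictors, which overloads it at about 43 expected responders

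*Protocol article*

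**What the plan says.** All references are to the protocol article.

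- **Statistical analysis.** Outcomes are compared primarily by t test or Mann-Whitney test (continuous) and Fisher's exact test (categorical). An adjusted analysis is then justified by the risk of chance imbalance in trials of fewer than 1000 patients, and "possible predictors of treatment outcome (i.e. known prognostic factors) will be included in a multivariate logistic/linear regression model". The factors are age at ESES recording, interval from recording to inclusion, baseline IQ and cognitive sum score, number of earlier drugs, and aetiology in six categories. The next sentence is "We will also include cytokine and autoantibody profiles as possible predictors".
- **Cytokine profiles and autoantibodies.** "A snapshot of around 100 cytokines will be analysed", at randomisation and at month 8. Seven autoantibody targets are named across the screening and the cell-based assays.
- **Background, secondary objectives.** Biomarkers, including immunological ones, are to be assessed "as potential predictors of disease activity and response to treatment with corticosteroids or clobazam". The Discussion paragraph of the abstract adds that biomarkers of treatment response would guide clinicians in early treatment.
- **Sample size calculation.** 116 evaluable patients, with 50% vs 25% success as the worked example, raised to 130 for 10% dropout.

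**The concern.** The text gives one model two jobs. Adjusting a treatment effect calls for a few strong baseline covariates. Searching for predictors calls for many candidates and some protection against overfitting. As written, the markers join the adjustment model, so each marker term draws on the same small number of responders that supports the adjusted treatment estimate.

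The second difficulty is the question being asked. A marker entered as a predictor of outcome shows which children do better whatever they receive. It does not show whether a child would do better on corticosteroids than on clobazam, and that is the part of the objective that would inform the choice between them.

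Two things are at stake: an adjusted estimate that may be unstable or impossible to obtain, and a biomarker result that could be read as a guide to treatment when it carries only prognostic information.

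**Working it through.** **1. Reproduce the plan's sample size.** Two proportions, 0.50 vs 0.25, two-sided alpha 5%, power 80%, pooled variance, no continuity correction:

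n per arm = [1.960·√(2·0.375·0.625) + 0.842·√(0.5·0.5 + 0.25·0.75)]² / 0.25² = (1.342 + 0.557)² / 0.0625 ≈ 57.7, so 58 per arm and 116 in total, as stated. 116/0.9 = 128.9, so 129; the article uses 130.

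**2. Expected responders.** 58·0.50 + 58·0.25 = 29 + 14.5 = 43.5.

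**3. Parameters, excluding the intercept.** Treatment 1; age, interval, IQ, sum score and number of drugs, each linear, 5; aetiology with six levels, 5. Total 11.

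**4. Load on the model at 116 patients.**

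| Model | Parameters | Responders per parameter (logistic) | Residual df (linear) |
|---|---|---|---|
| Treatment + listed factors | 11 | 43.5/11 = 4.0 | 116 − 11 − 1 = 104 |
| + 1 marker score | 12 | 3.6 | 103 |
| + 2 marker scores | 13 | 3.3 | 102 |
| + 100 cytokines | 111 | 0.4 | 4 |
| + 100 cytokines + 7 named autoantibodies | 118 | 0.4 | −3 |

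With 111 pure-noise predictors the expected R² of the linear model is 111/115 = 0.97. If all 130 children were complete, the first row would be 48.75/11 = 4.4 and the last would have 11 residual df.

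**5. Does the logistic model have a finite fit?** Complete or quasi-complete separation was checked by linear programming in 200 simulated trials of 116 patients, with independent normal markers unrelated to outcome (an assumption).

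- With 100 marker terms, separation occurred in 100% of trials.
- Without aetiology terms it occurred in 0% with 10 or 20 markers, 12% with 40 and 98.5% with 60.
- With an assumed 3% share for each of the metabolic, immune and infectious categories, the marker-free model was itself separated in 68%. Such separation concerns the rare category's coefficient first, and it is a reason to collapse aetiology.

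**6. Sensitivity to the success rates.** 50% vs 25% is only an example. At 75% vs 50% the rarer outcome (failure) again numbers 43.5. At the pooled-analysis rates in the Background it is smaller: 116 − 58·(0.75 + 0.59) = 38.3, or 3.5 per parameter; and 116 − 58·(0.81 + 0.68) = 29.6, or 2.7 per parameter.

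**7. Power for a treatment-by-marker term.** A main effect detectable with 80% power lies 1.960 + 0.842 = 2.802 standard errors from zero. For a marker splitting patients 50:50, the interaction has twice that standard error. An interaction of the same size therefore lies 1.401 standard errors away, and power = Φ(1.401 − 1.960) = Φ(−0.559) ≈ 29%.

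**The case against.** The strongest reply is that the text speaks of profiles, not of 100 separate terms; 100 is the size of the assay. A few summary scores can be fitted. That is right, and a flat statement that the model cannot be fitted is not supported. The article states no reduction, however, and even one or two scores add load to a model that starts at 4 responders per parameter.

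Next, variable selection, data reduction, multiplicity control and interaction terms are commonly left to an analysis plan that is not shown here. Their absence is not the point. The point is a stated rule: the factors and the marker profiles are to be included in a model motivated by chance imbalance. Followed literally, that rule performs badly at the trial's own size.

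Third, the model is logistic or linear, and the Sample size calculation allows the primary outcome to be analysed as continuous. Without markers the linear form has 116/11 = 10.5 patients per parameter and is workable. This stands: before any marker is added, the thin support concerns the logistic form.

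A reader might also infer three stronger things:

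- **That month-8 samples will predict the month-6 outcome.** The article does not say so. Change in inflammatory markers is listed as an outcome of its own, and there are also 18-month outcomes, which month 8 precedes.
- **That about five false-positive cytokines will arise from 100 tests at 5%.** The article describes no such one-at-a-time screen.
- **That the objective concerns only treatment choice.** Its wording also covers disease activity, for which prognostic main effects are appropriate.

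**Conclusion.** The point holds as a recommended change to a secondary analysis. On the article's own inputs there are about 43 responders for 11 parameters, about 4 each, before any biomarker enters. Marker scores lower that to 3.6 or 3.3. Separate entry of about 100 cytokines leaves no finite logistic fit and 4 residual degrees of freedom in the linear model, or none once the seven named autoantibodies are added.

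These figures assume 116 evaluable children, 50% vs 25% success, linear continuous terms and all six aetiology categories occurring. Other success rates taken from the article give the same count of the rarer outcome or a smaller one. The Discussion reports slower recruitment than expected, and a smaller sample would make the ratio worse.

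It would be wrong to conclude that the trial's main result is compromised: the primary comparisons are unadjusted and do not use this model. What suffers is the adjusted treatment estimate and the part of the biomarker objective that concerns response to one drug or the other, which marker main effects cannot address.

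**What to change.** 1. **Treatment-effect model.** Remove the biomarkers. Limit the model to treatment, the baseline value of the outcome analysed, age, and aetiology collapsed to two or three groups fixed in advance. That is 4 or 5 parameters, or 43.5/4 = 10.9 to 43.5/5 = 8.7 responders each. Randomisation is stratified by centre, so account for centre by a random effect or by stratification. Fixed effects for the 22 centres or 12 countries in Study setting would overload the model again: 5 + 21 = 26 parameters (1.7 responders each) or 5 + 11 = 16 (2.7 each).
2. **Biomarker analysis.** Run it separately, label it exploratory, and use baseline samples only. Include treatment-by-marker interaction terms, with either false-discovery-rate control or penalised regression.

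This alters wording only; no patients, visits or assays change. There are three costs. The interval to inclusion, the number of earlier drugs and the second baseline cognitive score are no longer adjusted for. Fewer nominal biomarker hits will be reported. Power for interactions stays low, about 29% for a 50:50 marker with an interaction as large as the detectable main effect, and less after multiplicity control, so a negative biomarker result should not be read as evidence that response does not differ.

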### Sample size calculation

A formal sample size calculation is hampered by the fact that no previous trials with these interventions have been performed. Our recently performed meta-analysis of published cases with epileptic encephalopathy with ESES provides the basis for estimating the difference in proportions of successfully treated patients that might be expected between corticosteroids and benzodiazepines. In our meta-analysis, treatment success was defined as improvement in EEG (at least 25% decrease in SWI) or cognition (10 IQ points or improvement defined by author). Differences in proportions were 25–30% between the two treatment groups in favour of corticosteroids. However, these results are of limited value because of the small sample size in the included studies and their mostly retrospective design.

In the RESCUE ESES study, we aim to include a total of 130 children, of whom 65 will be randomised to treatment with corticosteroids and 65 to clobazam. This sample size permits to detect a difference of 25% in the proportion of successfully treated patients between the two treatment arms (for example 50% vs 25%). In fact, 116 patients are needed to identify this difference with a power of 80% and a two-sided alpha of 5%, and we additionally account for a possible dropout rate of 10%.

As mentioned above, success is defined as improvement of 0.75 of the standard deviation of either IQ or the cognitive sum score. Differences of this magnitude have been reported in earlier observational (non-randomised) studies in this area [28]. Displaying the primary outcome as a dichotomous value (instead of a continuous value) will lead to a conservative estimation of the difference in effect. Therefore, our sample size calculation is likely to be an overestimation of the required number of patients for the continuous outcomes.

For continuous outcomes, we can detect standardised mean differences or Cohen’s *d* of around 0.5 (power = 80%, two-sided alpha of 5%). For Cohen’s *d*, an effect size of 0.2 to 0.3 is considered a “small” effect, around 0.5 a “medium” effect, and above 0.8 a “large” effect [29]. This means that “medium” effects on secondary outcomes can be detected by our trial including 130 children. Furthermore, as the primary outcome can also be displayed as a continuous variable (IQ or cognitive sum score), this also applies to analysis of the primary outcome as a continuous variable.

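### The 116 patients match an uncorrected normal-approximation calculation, but the named test is Fisher's exact test, which has about 74–78% power at that size, not 80%

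*Protocol article*

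**What the plan says.** The Sample size calculation section of the protocol article sizes the trial on a success proportion. It says "This sample size permits to detect a difference of 25% in the proportion of successfully treated patients between the two treatment arms", with rates given as "for example 50% vs 25"%, and then that "116 patients are needed to identify this difference with a power of 80% and a two-sided alpha of 5"%. On enrolment, "we aim to include a total of 130 children, of whom 65 will be randomised to treatment with corticosteroids and 65 to clobazam"; the step from 116 to 130 is explained by "we additionally account for a possible dropout rate of 10"%. The test or formula behind 116 is not named. The same section describes the sizing as resting on the dichotomous form of the primary outcome: "Displaying the primary outcome as a dichotomous value (instead of a continuous value) will lead to a conservative estimation of the difference in effect".

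The Statistical analysis section does name a test. "Categorical outcomes will be presented as proportions with 95% confidence intervals", and then: "These outcomes will primarily be compared between the two treatment groups using Fisher’s exact test". The Outcomes section gives each co-primary outcome a threshold for improvement, so the success proportion is a categorical outcome in this sense.

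**The concern.** A sample size is tied to a test. Fisher's exact test conditions on the table margins, and because its p-values are discrete it rejects less often than its nominal 5%. A number derived from a normal approximation without correction therefore gives less power when Fisher's test is used. If 116 comes from such a formula, the stated 80% is not the power of the planned comparison. Part of the margin meant for dropout would then be spent on the conservatism of the test. Slow recruitment, which the Discussion reports, makes that margin hard to replace.

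**Working it through.** **Inputs**, all from the protocol article: success rates 0.50 and 0.25; two-sided alpha 0.05 (z = 1.96); power 80% (z = 0.8416); 1:1 allocation; 116 evaluable, 130 randomised, 10% dropout; Fisher's exact test for categorical outcomes.

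**Step 1: reproduce 116.** The mean rate is (0.50 + 0.25)/2 = 0.375. The pooled formula without correction is

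n per arm = [1.96·√(2·0.375·0.625) + 0.8416·√(0.50·0.50 + 0.25·0.75)]² / 0.25² = 57.7, so 58 per arm and 116 in total.

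The stated figure is matched exactly. Other formulas:
- Arcsine: 57.3, so again 58 per arm and 116.
- Unpooled variance: 55 per arm, 110 in total.
- Continuity-corrected, which approximates Fisher's test: 66 per arm, 132 in total.

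Dropout: 116/0.9 = 128.9, so 129, consistent with 130 in two equal arms.

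**Step 2: power of Fisher's test.** For given arm sizes, take every possible 2×2 table, compute the usual two-sided Fisher p-value, and sum the binomial probabilities (success 0.50 and 0.25) of the tables with p ≤ 0.05. The arm with 50% success is listed first.

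| Evaluable | Split | Power, Fisher |
|---|---|---|
| 116 | 58/58 | 74.3% |
| 116 | 57/59 | 75.6% |
| 116 | 59/57 | 78.1% |
| 116 | 56/60 or 60/56 | 76.9% |
| 116 | 55/61 | 77.4% |
| 117 | 58/59 | 78.3% |
| 117 | 59/58 | 77.1% |
| 121 | 60/61 | 80.0% |
| 126 | 63/63 | 79.4% |
| 128 | 64/64 | 80.2% |
| 130 | 65/65 | 80.9% |

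The 117 rows are the protocol's own expectation: 130 × 0.9 = 117. Defining the two-sided p-value by doubling the smaller tail gives no higher power at 116 or 117 (for example 76.1% at 58/59).

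**Step 3: the uncorrected chi-square test.** The same enumeration at 58/58 gives 79.9%, which is the stated 80% after rounding.

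**Step 4: true type I error.** At 58/58, with a common success rate of 25%, 37.5% or 50%, Fisher's test rejects in 3.1–3.2% of trials and the uncorrected chi-square test in 4.8–5.2%. At 57/59 and 58/59, Fisher's true size is about 3.7–4.2%. This gap below 5% is where the power goes.

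**Step 5: the dropout allowance.** The allowance is 130 − 116 = 14 children. With equal arms, 80% needs 128 evaluable, so 128 − 116 = 12 of the 14 are taken up. Keeping both Fisher's test and a 10% allowance would need 128/0.9 = 142.2, that is 143 randomised, again for equal arms.

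**Step 6: other rates 25 points apart, 58/58.** Fisher's power is 72% at 60% vs 35%, about 83% at 40% vs 15%, and 74.3% at 75% vs 50% (by symmetry).

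**The case against.** The strongest reply has four parts.

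- **74% is nearly a worst case.** Exactly equal arms make Fisher's test most discrete. Ten percent dropout from 130 leaves 117, which cannot split equally, and the power is then 77–78%. This stands, and it is why the shortfall should be given as about 2–6 points. A reader might infer that the trial simply has 74% power; the figures do not support that as a general statement.
- **The rates are only an example.** This is true, and uncertainty about them can move power more than the choice of test does: at 55% vs 25%, a 30-point difference within the range the protocol reports from its meta-analysis, Fisher's power at 58/58 is 88.4%. But 50% against 25% is the only pair offered in support of 116, and the stated 80% has to be judged on it.
- **Other analyses are planned.** The protocol also allows a continuous analysis of the primary outcome and adds regression adjusted for prognostic factors. Neither suffers from Fisher's conservatism. Still, the 116 rests on the dichotomous outcome, and Fisher's test is the comparison named as the main one for it.
- **The error is on the safe side.** Fisher's test keeps the type I error below 5%. This stands and lowers the severity.

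A reader might also conclude that the arithmetic is wrong, or that 116 can only have come from a chi-square formula. Neither follows: 116 is correct for a standard uncorrected calculation, the arcsine formula gives it too, and the protocol does not say which was used.

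**Conclusion.** The point holds as a mismatch between sizing and analysis. At 50% vs 25% and 116–117 evaluable children, Fisher's exact test has about 74–78% power, depending on the split, against the stated 80%. None of the near-equal splits of 116 or 117 that were run reaches 80%.

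It would be too strong to say that 80% is reached only if all 130 are evaluable. Equal arms get there at 128, and a 60/61 split gets there at 121. The 128 evaluable and 143 randomised are equal-arm figures. Nor is the validity of the trial in question, since the loss is in power alone.

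The conclusion assumes that the success proportion is compared with Fisher's test as the Statistical analysis section says, that the usual two-sided p-value is used, and that the example rates apply. At lower success rates, such as 40% vs 15%, there is no shortfall; at 60% vs 35% it is larger. Severity: minor to moderate.

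**What to change.** Make one of two changes.

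1. In the Statistical analysis section, name the uncorrected chi-square test as the primary test for the success proportion, and keep Fisher's test for sparse tables such as rare adverse events. Power at 58/58 is then 79.9%, which agrees with the sample size section. The price is that the true size is no longer guaranteed to stay below 5% (4.8–5.2% at 58/58). A centre-stratified version, such as Mantel-Haenszel, would also reflect the randomisation, which is stratified by centre; its power was not computed here.
2. If Fisher's test is kept, restate the power in the Sample size calculation section as about 74–78% at 116 evaluable, for 50% vs 25%.

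In either case, state which formula gave 116. The cost is one or two sentences and no additional patients. The choice should be fixed before any comparison of outcomes by arm, including the planned interim analysis.

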Despite the good intentions of local investigators, announcements on congresses, in newsletters, on websites and RESCUE ESES newsletters and promotional material, recruitment of patients in the centres where the study was initiated has so far been slower than expected. No general reasons have become apparent, but a few possible explanations have been proposed. Some patients did not participate because they considered the study investigations time-consuming and were concerned that their treatment might be delayed. Others had a strong preference for one of the treatment arms, e.g. because of the ease of use of clobazam or presumed higher effectivity of corticosteroids. Furthermore, the investigators involved are only supported in trial management and not financially compensated for time spent on study procedures. In addition, some local investigators mentioned that it was difficult to influence local referral patterns and that they failed to promote referral of additional ESES patients for enrolment in the study.

To conclude, we believe that this study addresses an important open question and that the results may guide clinicians in choosing the best treatment for patients with epileptic encephalopathy with ESES.

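### The trial is sized on a dichotomised success endpoint, and the protocol leaves open whether that form or the more powerful continuous form of the same score decides the trial

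*Protocol article*

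**What the plan says.** All references are to the protocol article.

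- **Outcomes.** Both co-primary measures at 6 months carry a threshold: a gain of 10 points for IQ/DQ, and at least three quarters of an SD for the cognitive sum score. Change in IQ/DQ and in individual test results is listed separately as a secondary outcome at 6 and 18 months.
- **Sample size calculation.** The trial should "detect a difference of 25% in the proportion of successfully treated patients between the two treatment arms (for example 50% vs 25" per cent). The text continues that "116 patients are needed to identify this difference with a power of 80% and a two-sided alpha of 5" per cent, and "we additionally account for a possible dropout rate of 10" per cent, which leads to 130 children. Success there means a gain of 0.75 SD on either score. The section calls "Displaying the primary outcome as a dichotomous value (instead of a continuous value") conservative and says that the number is probably more than continuous outcomes need. It adds that a standardised difference of about 0.5 is detectable, and that this applies to the primary too, "as the primary outcome can also be displayed as a continuous variable (IQ or cognitive sum score").
- **Statistical analysis.** "Categorical outcomes will be presented as proportions with 95% confidence intervals" and are compared mainly by Fisher's exact test. Continuous outcomes are compared mainly by a t test or Mann-Whitney test. Regression models that include IQ and sum score at enrolment are planned as adjusted analyses. The section does not say which form of the primary outcome is decisive.
- **Discussion.** Recruitment "has so far been slower than expected".

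**The concern.** IQ/DQ and the sum score are measured on continuous scales. Cutting the change at a threshold treats a child who gains 9 points like one who loses 9, and a child who gains 11 like one who gains 30. The test on the resulting proportions usually needs more children for the same underlying effect. The protocol recognises this but presents it as caution in the sample size. That margin exists only if the continuous comparison is the deciding one. If the proportions decide, the trial has the power of the proportions test and no reserve.

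Two features make this matter here. Recruitment is slow, so the final number may be below 130, where the proportions test suffers most. The trial is also open-label with a planned interim look at the primary outcome, so two undecided forms of that outcome leave room to choose between them after results are known.

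**Working it through.** **Inputs from the protocol article (Sample size calculation; test from Statistical analysis).** Success 50% vs 25%; two-sided alpha 5%; power 80%; 116 evaluable, so 58 per arm; 10% dropout; 130 enrolled, 65 per arm; Fisher's exact test for proportions.

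**1. Reproduce the stated number.** With pooled variance and no continuity correction,

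n per arm = [1.96·√(2·0.375·0.625) + 0.842·√(0.25 + 0.1875)]² / 0.25² = 57.7, so 58 per arm and 116 in total. Then 116 / 0.9 = 128.9, so 129, rounded to 130 for equal arms. Both figures reproduce. The 116 belongs to an uncorrected chi-square test; the continuity-corrected formula gives 132.

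**2. Power of the planned test (exact binomial enumeration, 50% vs 25%).**

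| Per arm | Fisher | Uncorrected chi-square |
|---|---|---|
| 40 | 56% | – |
| 58 | 74% | 80% |
| 65 (no dropout) | 81% | 85% |

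At 58 per arm, the drop from 80% to 74% comes from the choice of test, not from the dichotomy.

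**3. The same effect on the continuous scale, assuming a normal shift with equal SD and a cut on one score.** d = z(0.50) − z(0.25) = 0 − (−0.674) = 0.674.

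- t-test power: 95% at 58 per arm, 97% at 65, 85% at 40.
- n for 80% power: the normal approximation gives 2·(1.96 + 0.842)² / 0.674² = 34.5; the t test needs 36 per arm, or 72 in total.
- Relative saving against 116: 1 − 72/116 = 38%.

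**4. The same success rates from a responder mixture (illustrative, not from the documents).** Non-responders have mean change 0, responders +15 or +20 points, within-group SD 6 to 8, cut at 10 points. The responder shares are set so that success is 50% and 25%. Two corners:

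- +20, SD 6: success is 95.2% in responders and 4.8% in non-responders, so the shares are (0.50 − 0.048)/0.904 = 50% and (0.25 − 0.048)/0.904 = 22.4%. Mean difference 20·(0.500 − 0.224) = 5.5. Variances 36 + 400·0.25 = 136 and 36 + 400·0.224·0.776 = 105.5. d = 5.5/√120.8 = 0.50.
- +15, SD 8: success is 73.4% and 10.6%, so the shares are 62.8% and 23.0%. Mean difference 15·0.398 = 6.0. Variances 64 + 225·0.628·0.372 = 116.6 and 64 + 225·0.230·0.770 = 103.8. d = 6.0/√110.2 = 0.57.

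Simulated t-test power at 58 per arm runs from 76% (first corner) to 85% (second). At 40 per arm it runs from 60% to 70%, against 56% for Fisher.

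**5. Success on either score.** With two normal scores and equal shifts, the single-score d behind 50% vs 25% is 0.60 to 0.66 (correlation 0.9 down to 0.3 or the reverse; range assumed), and t-test power at 40 per arm is 75% to 83% rather than 85%.

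**6. The protocol's continuous figure.** Detectable d at 80% power is 0.495 at 65 per arm and 0.525 at 58 per arm, so the stated value of about 0.5 is right.

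**The case against.** The strongest case on the other side has four parts.

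- **Nothing is thrown away.** A reader might infer that the trial discards 38% of its information. The documents do not support that: change in IQ/DQ is a secondary outcome, a test for continuous outcomes is planned, and the primary may also be shown continuously. If the deciding form is open, the loss is also not yet incurred. This stands, and it limits the point to the success comparison and to the unfixed choice.
- **The inefficiency is disclosed.** A reader might say that the word conservative hides a loss of power. It does not: the same section states that continuous outcomes would probably need fewer children. What remains is that the protocol notes the inefficiency without acting on it.
- **The gain depends on the model.** The 95% and the 38% require a pure normal shift on one score. The protocol's own hypothesis speaks of responders, and under a responder mixture the t test gains between 2 and 11 points over Fisher's 74%. At the lower end its 76% is below the 80% of an uncorrected chi-square test. This stands, so the gain has to be given as a range.
- **A responder endpoint is legitimate, and changing it has a price.** It ties to the stated hypothesis and to the meta-analysis, the only source for the effect size. The trial is registered, recruiting and open-label, so a late change could look like outcome switching. This stands as a cost and determines when the change can be made.

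It is also tempting to conclude that the trial will stop short of 130. The article reports slow recruitment but gives no projection; 40 per arm is only an illustration.

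**Conclusion.** The point holds as an improvement to the choice of primary analysis, not as an error in the sample size, whose 116 and 130 reproduce. The trial is sized on a cut of scores that it measures continuously, and the article does not say which form decides. At the protocol's example rates and 58 evaluable per arm, the named Fisher test has 74% power, not 80%. The continuous comparison has about 95% under a normal shift with equal SD, and about 76% to 85% under the responder mixtures tried. In none of the scenarios checked was it below Fisher. The Fisher figure rests only on the protocol's own rates and test; the continuous figures rest on assumed distributions, because the article gives no SD of change.

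**What to change.** Before any outcome data are examined, including at the interim analysis planned when half the required patients have a primary outcome:

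- Name the baseline-adjusted mean difference between arms at 6 months in IQ/DQ as the primary analysis, and likewise in the cognitive sum score if it stays co-primary. The baseline scores are already listed as covariates in the Statistical analysis section.
- Report the proportions improved, with confidence intervals, as supportive.
- Keep 130 children. Restate the Sample size calculation on the continuous scale: 80% power for d of about 0.5 (0.495 at 65 per arm, 0.525 at 58).
- For the responder comparison, give 74% as the power of Fisher's test at 58 per arm.

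The change uses the same assessments and needs no further patients. It costs a dated amendment, in a trial where national approvals have already been slow. The responder rate, which clinicians read easily and which links to the hypothesis and the meta-analysis, becomes secondary.
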